#### Visit 2: skin structure and morphology

The minimally invasive skin punch biopsy technique, used for diagnostic investigation of skin blood vessels, sweat glands and nerves (30), will be performed according to international consensus guidelines (31, 32). Upon arrival, intradermal injection of local anaesthesia (Marcain) will be administered to a non-venous, non-hairy, tattoo-free location on the non-dominant forearm (site assessed in visit 1). A 3 mm diameter biopsy will be sampled using a punch biopsy tool (Stiefel, Maidenhead, U.K.) to an approximate depth of 5 mm (Figure 2). Biopsies will be placed immediately into a periodate-lysine-paraformaldehyde (PLP) fixative and stored for 24 h at 4°C, following which it will be cryoprotected in 15% sucrose for 24–72 h at 4°C, before being frozen in liquid nitrogen and stored at −80°C, adhering to all Human Tissue Act (2004) legislation and LJMU procedures.

**Figure 2 F2:**
[figure not shown]
Skin punch biopsy methodology.

Frozen samples will be cut (∼50 microns) and stained with fluorescein-labelled Ulex europaeus agglutinin I, an endothelium-specific antibody (33), and with anti-protein gene product 9.5 (1:1000, anti-PGP 9.5, Chemicon International Inc.), an antibody used to visualise nerve fibres around sweat glands and blood vessels in human skin.

Confocal microscopic imaging of samples (optical sections will be acquired at 2–4 μm intervals throughout the 50 μm section as a z-stack and will be projected in 3D images, Zeiss Axioplan 2, Germany) will subsequently be analysed using ImageJ software (32) to quantify the number and size of the stained blood vessels and the size of the secretory coils of the sweat glands, as well as the number of nerve fibres around the sweat gland within the samples (Figure 2). For between groups analyses (e.g., pre- vs. postmenopausal cohorts), data will be analysed using a one-way ANOVA.

### Study withdrawal

Each participant has the right to withdraw from the study at any time with no obligation to provide a reason. If provided, reasons for withdrawal will be retained, but personal data will be disposed of. Furthermore, participants may be withdrawn from the study by the research team at any time if the research team considers it necessary for any reason including:
•Ineligibility (either arising during the study or retrospectively having been overlooked at screening).•Significant non-compliance with study requirements.•Withdrawal of consent.Withdrawal from the study will not result in exclusion of the participant's data from analysis, as all data will be pseudonymised. Withdrawn participants will not be replaced. Participants will be asked for their reasoning behind withdrawal, either via email or telephone call and the reason will be recorded in an end of study case report; participants are able to give no reason for withdrawal.

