**Methods and analysis:**

This is a single-centre multi-cohort observational study. Participants will attend the laboratory at Liverpool John Moores University (LJMU) on two separate occasions, ∼7 days apart. Visit 1 will consist of anthropometry, a blood sample and assessment of post-ganglionic skin blood vessel and sweat gland responsiveness via cutaneous microdialysis. At visit 2, participants will return for a skin punch biopsy. A between groups statistical analysis of the pre- and postmenopausal cohorts will be conducted in a blinded manner.

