### Sample size calculation

Based on previously reported differences in post-ganglionic skin blood flow responses between postmenopausal women with and without hot flushes (17–19), a power (1-β) of 0.9 and an effect size of 1, 24 postmenopausal women (12 who experience hot flushes and 12 who do not) and 12 premenopausal women will be recruited for this study.

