### Eligibility criteria

Potential participants will exclude themselves based upon the detailed inclusion/exclusion criteria (Table 1) provided on recruitment material and the PIS. These criteria reflect the practical requirements of the study, to ensure that research findings are valid and to ensure the safety of participants. Participants will be consented and screened, consisting of medical history and details of current medications. Postmenopausal participants will complete a 7-day hot flush diary (25). Members of the research team will review completed screening information to confirm eligibility to participate.

**Table 1 T1:** Detailed inclusion and exclusion criteria.

Detailed inclusion criteria		
Postmenopausal + Hot Flush	Postmenopausal	Premenopausal
• Female • Aged 45–65 years • Amenorrhoeic for >6 months • >4 Hot flushes per day • Not on medication or treatments to alleviate hot flushes e.g., HRT	• Female • Aged 45–65 years • Amenorrhoeic for >6 months	• Female • Aged 18–40 years • Eumenorrheic
AND		
• Healthy • Non-smoker/non-vaper • BMI 18–30 kg/m^2^ • No history of cardiovascular or respiratory disease • No history of metabolic diseases e.g., type II diabetes • Drink <14 units of alcohol per week • Participant is willing and able to give informed consent for participation in the study.		
Detailed exclusion criteria		
• Cannot readily read and understand English • Aged <18 years, 41–44 years or >65 years • Male • Current smoker/vaper • BMI <18 or >30 kg/m^2^ • Medical history of cardiovascular/respiratory disease • Medical history of metabolic disease e.g., type II diabetes • Drink >15 units of alcohol per week • Vaccination (<1 week) due to induced systemic inflammatory reaction • Local forearm infection • Allergy to local anaesthetic/Marcaine/amide-group anaesthetics • Currently pregnant, or planning on becoming pregnant • <6 Months postpartum or stopped breast feeding <1 month before recruitment • On medication or treatments to alleviate hot flushes or have taken such medication/treatments within the previous 6 months e.g., HRT		

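### Women withdrawn as ineligible stay in the analysis without exception; those who failed a criterion that defines their group should leave the primary analysis

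*Protocol article*

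**What the plan says.** The Study withdrawal section of the protocol article lists grounds on which the research team may withdraw a participant. One is "Ineligibility (either arising during the study or retrospectively having been overlooked at screening"; another is significant non-compliance. One rule then covers every ground: "Withdrawal from the study will not result in exclusion of the participant's data from analysis, as all data will be pseudonymised". The next sentence adds: "Withdrawn participants will not be replaced".

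The abstract describes the design: "This is a single-centre multi-cohort observational study". Group membership comes from Table 1. Both postmenopausal groups are aged 45–65 and amenorrhoeic for more than 6 months, and the hot-flush group also has more than 4 flushes per day. The premenopausal group is aged 18–40 and eumenorrheic. Treatment for hot flushes, current or in the previous 6 months, excludes a woman from any group. The Eligibility criteria section says that the criteria serve, among other purposes, "to ensure that research findings are valid". The Sample size calculation section sets the numbers: "24 postmenopausal women (12 who experience hot flushes and 12 who do not) and 12 premenopausal women will be recruited".

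**The concern.** The reason given for keeping the data is that they carry a code in place of a name. That may explain why data can be held after a woman leaves. It does not explain why data from a woman who never met her group's definition should count towards that group's mean.

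The design supplies no other reason. In a randomised trial, keeping all participants protects the comparison that randomisation created. Here the groups are formed by the eligibility criteria, so there is no such comparison to protect. The criteria are there partly for validity, and the withdrawal rule sets that aside for the very women known to have failed them.

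The protocol itself foresees discovery after the event. Screening rests on self-exclusion, medical history, current medication and a self-reported 7-day diary, and the limitations section accepts that the diary is open to reporting bias. With 12 women in a group, each one carries 1/12, or 8.3%, of the group mean.

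**Working it through.** **Inputs.** Group sizes are 12, 12 and 12. The planning values are "a power (1-β) of 0.9 and an effect size of 1", for "differences in post-ganglionic skin blood flow responses between postmenopausal women with and without hot flushes" (Sample size calculation). I read the effect size as a standardised difference, d = 1 with SD 1. Neither the significance level nor the sidedness is stated, so two-sided 5% is assumed.

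**1. The plan's own figure.** For two independent means, n per group = 2(1.960 + 1.282)² / 1² = 21.02, so 22. The exact t-test needs 22.02, so 23. A one-sided test needs 18. The stated 12 is not reproduced. At 12 versus 12:
- two-sided t-test: power 0.65 (normal approximation 0.69);
- one-sided t-test: power 0.77.

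This shortfall is a separate matter. It is used here only as the baseline, and the bias in step 2 does not depend on it.

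**2. Effect of keeping misplaced women.** Suppose k of the 12 women in the hot-flush group truly respond like the comparison group. The expected difference is then

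(12 − k)/12 × 1 + k/12 × 0 = 1 − k/12.

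- k = 1: 0.917
- k = 2: 0.833
- k = 3: 0.750

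Mixing two kinds of women also widens the spread within the group. Its expected sample variance rises from 1 to 1 + k(12 − k)/(12 × 11):
- k = 1: 1 + 11/132 = 1.083
- k = 2: 1 + 20/132 = 1.152

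A shortcut that lowers d alone gives power 0.574 and 0.497 for k = 1 and 2. It leaves out this extra variance and so understates the loss.

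**3. Power, by simulation.** 200,000 two-sided t-tests were run per row, with a true difference of 1 SD.

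| k | Kept: expected difference | Kept: power | Excluded, not replaced: expected difference | Excluded: power |
|---|---|---|---|---|
| 0 | 1.00 | 0.65 | 1.00 | 0.65 |
| 1 | 0.92 | 0.56 | 1.00 | 0.63 |
| 2 | 0.83 | 0.47 | 1.00 | 0.60 |
| 3 | 0.75 | 0.38 | 1.00 | 0.58 |

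For one woman, exclusion gains 0.63 − 0.56 = 0.07 in power and removes the bias. For two, it gains 0.60 − 0.47 = 0.13.

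**4. Other kinds of ineligibility.** Suppose a breach shifts one woman's response by δ SD from her group's mean. The contrast (hot-flush minus comparison) moves by +δ/12 if she is in the hot-flush group and by −δ/12 if she is in the comparison group. With δ = −1, that is −0.083 or +0.083. The documents give neither the sign nor the size of δ for cardiovascular or metabolic disease or for hot-flush treatment, so the direction cannot be fixed.

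**The case against.** Several points on the other side are sound.

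- **Not every ineligible woman is misclassified.** A reader might infer that anyone withdrawn as ineligible contaminates a group. Table 1 does not support that. BMI, alcohol, recent vaccination, anaesthetic allergy and disease history define no group. A breach of these is at most a confounding or validity problem.
- **The bias need not run towards no difference.** It does when the woman truly belongs to the comparison distribution, as step 2 assumes. For hot-flush treatment or disease it could go either way (step 4).
- **The plain postmenopausal column sets no limit on flushes.** A woman with flushes in that group is not ineligible as Table 1 is written, so the withdrawal rule does not reach her. The flush-frequency example works only for the hot-flush group.
- **The rule does not say under which label a withdrawn woman is analysed.** A hot-flush participant found to have too few flushes would meet the plain postmenopausal column, and the text does not forbid moving her. It does not provide for it either. Nor does moving help a woman aged 41–44 or one on hot-flush treatment, since neither fits any group.
- **Timing matters.** Ineligibility that arises after visit 1 need not spoil visit 1 data.
- **The harm is conditional.** A woman must pass self-exclusion, history, medication review, diary and team review, give data, and only then be found ineligible. The documents give no rate for this, and nothing in them shows that one or two in 12 is likely.
- **Non-replacement is a resource choice.** It does not cause the bias. Each replacement would mean another microdialysis visit of 3–4 hours and a biopsy.

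One defence does not stand. An analysis plan that is not shown might define analysis sets, but to exclude these women it would have to contradict a sentence that the protocol states without exception. This is a rule badly fixed, not a detail left for later.

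**Conclusion.** The point holds in a bounded form. The protocol keeps the data of every withdrawn woman in the analysis, including women whose ineligibility was missed at screening, and supports this only with a privacy reason. In a non-randomised comparison of groups of 12, a woman who failed a group-defining criterion when measured (age or menstrual status, flush frequency in the hot-flush group, hot-flush treatment) would bias the contrast if kept in that group.

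The size rests on the assumptions used in steps 2 and 3: a 1 SD true difference, two-sided 5%, and misplaced women who respond like the comparator. Under them, exclusion is better than retention on both bias and power, even with no replacement. Other ineligibility is possible confounding of unknown direction. The documents do not support saying that contamination will occur, that it always dilutes the difference, or that the bar on replacement is itself an error.

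**What to change.** Rewrite the data rule in the Study withdrawal section so that ineligibility is handled apart from other withdrawal:

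1. Exclude from the primary analysis women found not to have met, at the time of measurement, a group-defining criterion (age or menstrual status, flush frequency in the hot-flush group, hot-flush treatment) or a vascular-function criterion (cardiovascular or metabolic disease).
2. Take that decision blind to outcome and group, from the eligibility record and before the analysis groups are unblinded. This fits the blinded between-group analysis already promised.
3. Keep the data of eligible women who withdraw, and data validly collected before ineligibility arose.
4. Report a sensitivity analysis that includes all participants.

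The cost is one paragraph and one extra analysis, with no added visits or biopsies. The downside is a slightly smaller primary analysis set: with one woman excluded from one group, 11 versus 12 and power of about 0.63 against 0.65 for the full groups. No replacement is needed.

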### Experimental design

This is a parallel group design where participants will attend the laboratory on two separate occasions. The first visit will consist of anthropometric measurements and a blood sample, followed by assessment of post-ganglionic skin blood vessel and sweat gland responsiveness (cutaneous microdialysis). At the second visit (∼7 days later), participants will undergo a skin punch biopsy.

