**Figure 1 F1:**
[figure not shown]
Illustration of the microdialysis technique and apparatus. Created in BioRender. [name] (2025). https://BioRender.com/ouwrev6.

Following microdialysis membrane placement and allowing for its associated hyperaemic response to subside (≥90 min), baseline CVC and SR will be collected for 5 min. Each membrane will subsequently be randomly assigned and perfused with one of the following: increasing doses of CGRP (1 × 10^−11^–10^−4^; 8 doses at 10-fold increments) dissolved in Ringer's solution, acetylcholine (Ach; 1 × 10^−7^-1M; 8 doses at 10-fold increments) dissolved in Ringer's solution, or sodium nitroprusside (SNP; 1 × 10^−7^-50 mM; 8 doses at 10-fold increments) dissolved in Ringer's solution. Each dose will be administered for 7 min (1 min at a perfusion rate of 5 µl/min and 6 min at 2 µl/min). Following the last dose, 50 mM SNP will be perfused through each membrane for 10 min to initiate peak vasodilation at each of the assessed sites (29).

Data will be continuously sampled at 50 Hz (PowerLab, ADInstruments, Oxford, UK) and recorded online (LabChart, ADInstruments, Colorado Springs, Colorado, USA). For each dose, CVC and SR will be averaged at 10 s intervals, and the 60 s average around the maximum 10 s value from each stage will be selected for analysis (29).

A between groups statistical analysis of the pre- and postmenopausal cohorts will be conducted in a blind manner. Exploratory analyses using a linear mixed model with fixed effects of drug dose (cutaneous microdialysis) and/or group will be conducted. Dose-response curves for CVC and SR at each of the three microdialysis sites will be constructed using a nonlinear fitting technique, from which the effective concentration causing 50% of the maximal response (EC_50_) will be identified (Prism, GraphPad Software). *Post hoc* comparisons across drug doses or between groups will be completed using Bonferroni adjusted LSD. Effect estimates with a 95% confidence interval for differences between groups, as well as changes within groups over drug doses, will be reported.

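### Power of 0.9 is stated for 12 women recruited per group, with no stated loss allowance and no replacement; 12 v 12 gives about 65% at 1 SD, and each loss before the biopsy lowers the structural comparison further

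*Protocol article*

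**What the plan says.** All references are to the protocol article.

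- **Sample size calculation.** The basis is "previously reported differences in post-ganglionic skin blood flow responses between postmenopausal women with and without hot flushes", with "a power (1-β) of 0.9 and an effect size of 1". From this, "24 postmenopausal women (12 who experience hot flushes and 12 who do not) and 12 premenopausal women will be recruited for this study". These are intake numbers. The section states no allowance for loss, no significance level and no type of effect size.
- **Study withdrawal.** "Withdrawn participants will not be replaced". The same section keeps what has been collected: "Withdrawal from the study will not result in exclusion of the participant's data from analysis". Women may leave freely, and the team may withdraw them, for instance for ineligibility or non-compliance.
- **Primary outcomes.** Microvascular and sudomotor function are measured at visit 1. Blood vessel and sweat gland size is also primary and comes from the biopsy.
- **Experimental design.** "At the second visit (∼7 days later), participants will undergo a skin punch biopsy".
- **Study limitations.** Power is conceded to be possibly limited because 36 is a small sample, chiefly for small differences. Loss of participants is not mentioned.

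**The concern.** The number that carries the stated power is the number recruited. The text shows no reserve above it, and the withdrawal rule closes the one other way of keeping it. The structural primary outcome is the most exposed, because it needs a second attendance for an invasive procedure, and keeping a woman's earlier data cannot supply a missing biopsy. The link between function and structure named in the Discussion needs both visits and is exposed in the same way.

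What is at stake is whether readers can rely on the 0.9. If 12 per group does not give it even with complete data, a null result will be read as stronger evidence of no difference than the design can provide. Unreplaced losses widen that gap.

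**Working it through.** **Inputs**

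- From Sample size calculation: power 0.90, effect size 1, 12 recruited per group.
- Assumed: effect size 1 is a standardised mean difference d between two independent groups. The comparison named there is between two groups of postmenopausal women.
- Assumed: two-sided 5%, in line with "Effect estimates with a 95% confidence interval for differences between groups" in the visit 1 analysis paragraph.
- Assumed: loss before biopsy of 5%, 10% or 20%, independent between women. The document gives no rate.

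**Step 1. Reproduce the stated figure.** The normal approximation is n per group = 2(z₀.₉₇₅ + z₀.₉₀)²/d² = 2(1.960 + 1.282)²/1² = 21.02, so 22. The exact t calculation gives 23. The stated 12 is not reproduced. Other readings:

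| Reading | Result |
|---|---|
| Two groups, one-sided 5% | 18 per group needed; power 0.77 at 12 (t) |
| Two groups, Bonferroni 0.05/3, two-sided | 29 per group needed (t); power 0.46 at 12 |
| Paired or one-sample t, two-sided 5% | 13 needed; power 0.88 at 12, but the groups are independent |
| Three-group ANOVA, f = 0.5 | power 0.73 at 12 per group |
| Three-group ANOVA, f = 1 | 6 per group needed |

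**Step 2. Power at d = 1 as groups shrink.** By the normal approximation, power = Φ(d√(n/2) − 1.960). At n = 12 this is Φ(2.449 − 1.960) = Φ(0.489) = 0.69. The noncentral t, with noncentrality d√(n/2) and 2n − 2 degrees of freedom, gives:

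| Women per group | Power at d = 1 | d detectable with 90% power |
|---|---|---|
| 12 | 0.65 | 1.39 |
| 11 | 0.61 | 1.45 |
| 10 | 0.56 | 1.53 |
| 9 | 0.51 | 1.63 |

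**Step 3. What loss does to the biopsy groups.** Expected completers per group are 12(1 − p). The chance that a given group loses at least one woman is 1 − (1 − p)¹².

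| Assumed loss p | Expected completers per group | Chance a group falls below 12 |
|---|---|---|
| 5% | 11.4 | 1 − 0.95¹² = 46% |
| 10% | 10.8 | 1 − 0.90¹² = 72% |
| 20% | 9.6 | 1 − 0.80¹² = 93% |

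**Step 4. Which outcomes are affected.** A woman lost between visits keeps her visit 1 data, so the two function outcomes lose only women who leave before or during visit 1. The structural outcome loses both kinds.

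**Step 5. Would protecting 12 repair the figure?** No. Keeping 12 completers means recruiting 12/(1 − p), that is 13 per group at 5% loss, 14 at 10% and 15 at 20%. Power at d = 1 would then be back at 0.65.

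**The case against.** **No loss rate is given, and the visits are only about 7 days apart.** This stands. A reader might infer that the analysed groups are bound to fall below 12, but the document does not support that. The shortfall depends on at least one loss.

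**The powered outcome is skin blood flow at visit 1, and withdrawn women's data are kept.** This also stands. A missed biopsy breaks no stated power, because none is stated for structure. But structure is listed as primary and rests on the same 12 per group, with nothing said about what that number can detect.

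**The effect size may be an ANOVA f of 1, and then 12 is ample.** This cannot be excluded, since the type is not named. It would be a very large effect. For three equally spaced means with range a, f = a/√6, so a = 2.45 SD; for two equal means and one apart, f = a√2/3, so a = 2.12 SD. The section also names a two-group difference as its basis.

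**An article condenses the full protocol.** Fair. One can say that no allowance is stated, not that none was made. The no-replacement rule and the 0.9 are nonetheless positive statements in the text.

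**The limitations already concede low power.** Only for the full 36, and chiefly for small differences. One SD is not small.

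**Not replacing is a legitimate choice.** It is. It limits how many volunteers undergo the procedures, and replacement would not correct selective loss. Its usual purpose of protecting a randomised comparison does not apply here, because the groups are defined by menopausal and hot-flush status. That makes replacement possible, not obligatory.

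A reader might also infer that a short-lived exclusion, such as "Vaccination (<1 week) due to induced systemic inflammatory reaction", must turn into a permanent loss. The withdrawal section leaves removal to the team's judgement, so that does not follow.

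**Conclusion.** The point holds in a limited form. Under the most natural reading (d = 1, two independent groups, two-sided 5%), 12 per group gives about 65% power, or 69% by the normal approximation, against the stated 0.9 before anyone is lost. Any loss before visit 2 leaves that group's structural outcome with fewer than 12, and nothing in the text makes this good. One loss per group takes power at 1 SD to about 61%, two to about 56%. The marginal cost of a single loss is modest; the larger fault is the stated figure itself. The function outcomes are largely protected from loss between visits.

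The conclusion rests on the assumed effect-size type, significance level and loss range. It does not rest on loss being certain, and it does not show that the no-replacement rule is wrong in itself.

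**What to change.** Amend Sample size calculation so that it:

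1. says that 12 per group is the number recruited;
2. names the type of effect size, the significance level and the comparison;
3. gives the assumed loss rate before visit 1 data and before the biopsy;
4. restates power, or the detectable difference, for the number expected to complete, separately for the visit 1 function outcomes and the visit 2 structure outcome.

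Possible wording, to be filled with the sponsor's own loss rates: *Twelve women will be recruited to each group. Assuming no loss before visit 1 and 10% loss before the biopsy, about 12 per group are expected for function and 11 for structure (10.8 before rounding). In a two-sided 5% comparison of two groups these numbers give 90% power for differences of 1.39 and 1.45 SD, and about 65% and 61% power for 1 SD.* If 10 completers are expected, the structure figures become 1.53 SD and about 56%.

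The cost is a less favourable stated figure. No procedure or recruitment target changes.

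Replacement within the same group, up to the planned 12, remains open to the sponsor as an option. It means enrolling more women (13 per group at 5% loss, 14 at 10%, 15 at 20%), and no recruitment rate is given to show that this fits the 12 months. It would preserve 12 completers but not provide 90% power at 1 SD.
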